## Abstract

**Background:**

Animal studies have reported an increase in pelvic floor muscle stiffness during pregnancy, which might be a protective process against perineal trauma at delivery. Our main objective is to describe the changes in the elastic properties of the pelvic floor muscles (*levator ani,* external anal sphincter) during human pregnancy using shear wave elastography (SWE) technology. Secondary objectives are as follows: i) to look for specific changes of the pelvic floor muscles compared to peripheral muscles; ii) to determine whether an association between the elastic properties of the *levator ani* and perineal clinical and B-mode ultrasound measures exists; and iii) to provide explorative data about an association between pelvic floor muscle characteristics and the risk of perineal tears.

**Methods:**

Our prospective monocentric study will involve three visits (14–18, 24–28, and 34–38 weeks of pregnancy) and include nulliparous women older than 18 years, with a normal pregnancy and a body mass index (BMI) lower than 35 kg.m^− 2^. Each visit will consist of a clinical pelvic floor assessment (using the Pelvic Organ Prolapse Quantification system), an ultrasound perineal measure of the anteroposterior hiatal diameter and SWE assessment of the *levator ani* and the external anal sphincter muscles (at rest, during the Valsalva maneuver and during pelvic floor contraction), and SWE assessment of both the *biceps brachii* and the *gastrocnemius medialis* (at rest, extension and contraction). We will collect data about the mode of delivery and the occurrence of perineal tears. We will investigate changes in continuous variables collected using the Friedman test. We will look for an association between the elastic properties of the *levator ani* muscle and clinical / ultrasound measures using a Spearman test at each trimester. We will investigate the association between the elastic properties of the pelvic floor muscles and perineal tear occurrence using a multivariate analysis with logistic regression.

**Discussion:**

This study will provide original in vivo human data about the biomechanical changes of pregnant women’s pelvic floor. The results may lead to an individualized risk assessment of perineal trauma at childbirth.

**Trial registration:**

This study was registered on https://clinicaltrials.gov on July 26, 2018 (NCT03602196).

## Background

Perineal trauma is a frequent complication of childbirth, which may lead to several pelvic floor disorders, such as anal incontinence, urinary incontinence, pelvic organ prolapse and sexual dysfunction [1–4] In the most severe cases, perineal trauma could involve an obstetric anal sphincter injury (OASI) (rupture of the external anal sphincter and, worse still, opening of the rectal mucosae) and/or levator avulsion. OASI, which occurs in nearly 5% of first deliveries, is associated with postnatal anal incontinence and dyspareunia [1]. Levator avulsion, which occurs in nearly 10% of first deliveries, is associated with pelvic organ prolapse and sexual dysfunction [3]. These injuries are associated with trauma of the pelvic floor muscles at vaginal delivery during which these muscles are overstretched, up to three times their initial length [5]. Several risk factors are described in the literature (forceps delivery, fetal macrosomia, etc.) However, the occurrence of these complications remains very difficult to predict [1–4]. It is likely that the risk of pelvic floor trauma can be influenced by intrinsic characteristics of the pelvic floor muscles and their ability to lengthen sufficiently to enable passage of the fetus through the birth canal without being damaged. Identifying women with a high risk of perineal trauma antenatally would enable clinicians to propose individualized counseling and preventive strategies for these women.

Few studies have indicated that some intrinsic biomechanical characteristics of pregnant women could be associated with the risk of perineal trauma [6–8]. In a recent prospective study, we reported an association between peripheral ligamentous laxity (assessed at the metacarpophalangeal joint) and the risk of OASI. In that study, the women with the greatest ligamentous laxity had the greatest risk of OASI [8]. This result supports the hypothesis of an association between a woman’s individual biomechanical characteristics and her risk of perineal trauma. However, the main limitation of this study was that it was designed to analyze data about an upper limb joint, which is probably very different from pelvic floor muscle tissues [8].

Data about changes in intrinsic characteristics of women’s pelvic floor muscles during pregnancy has mainly originated from experiments on rats [9–11]. Some authors have reported that an increase in muscular fiber length and an increase in pelvic floor muscle stiffness occurs during pregnancy, while no changes were reported for peripheral muscles [9–11]. This could be explained by the increase in mechanical loading (force due to gravity of growing fetus) applied to pelvic floor muscles during pregnancy [10]. This increase in elastic modulus may be a protective process from perineal trauma. On rats, studies reported an increase during pregnancy in both fiber length and stiffness measured at a given sarcomere length [9, 10]. These changes could be interpreted consequently from the increase of loading. The increase in fiber length was thought as a mechanism to limit the fiber strain that can cause injury. The increase in stiffness was thought to be related to extracellular matrix content and would likely reduce the risk of injury due to large strain that occurs during parturition [5, 9]. This is supported by a higher ultimate stress in biological tissues that have higher stiffness [12]. These data about animal experimentation need to be read with caution because there is no data proven that these phenomena occur in a same way in women.

To date, several techniques have been described to assess the in vivo elastic properties of the pelvic floor muscles (vaginal elastometry, tactile imaging, elastography) [13, 14]. One of the most relevant techniques is shear wave elastography (SWE), which allows a direct, quantitative and noninvasive assessment of the muscles [15]. Recently, we reported the feasibility of an in vivo assessment of the elastic properties of the *levator ani* muscle using this technique (100% of procedures allowing a visualization of the levator ani muscle and a measure of elastic properties in women with a lower than 35Kg.m^− 2^ body mass index) [13].

In accordance with animal experimentation, we hypothesize that there are changes in elastic properties of women’s pelvic floor through pregnancy and that SWE is relevant to follow these changes [9, 10]. They might be specific to pelvic floor muscles without, or less, significant changes for peripheral muscles such as *biceps brachii* or *gastrocnemius medialis*. Finally, the hypothetical changes in elastic properties of women’s pelvic floor may be associated with their intrinsic risk of perineal trauma at childbirth. Indeed, during vaginal delivery, a major strain is applied to pelvic floor muscles which are stretched up to 3 times their initial length [5, 16]. Thus, intrinsic elastic properties of pelvic floor muscles may be associated with their ability to support this strain without being damaged.

Our main objective is to describe the changes in the elastic properties of the pelvic floor muscles (*levator ani,* external anal sphincter) during human pregnancy using shear wave elastography (SWE) technology. The secondary objectives are as follows: i) to look for specific changes of the pelvic floor muscles compared to peripheral muscles; ii) to determine whether an association between the elastic properties of the *levator ani* and perineal clinical and B-mode ultrasound measures exists; and iii) to provide explorative data about an association between pelvic floor muscle characteristics and the risk of perineal tears.

## Methods

### Design

The ELASTOPELV study will be a prospective, longitudinal, monocentric study. The scheme of the study will involve 3 visits during pregnancy: the first one between 14 and 18 weeks, the second between 24 and 28 weeks and the last between 34 and 38 weeks of pregnancy (Fig. 1). For each of these three visits, the protocol will follow these steps: clinical perineal assessment, ultrasound B-mode perineal assessment, SWE assessment of the *levator ani* muscle, the external anal sphincter, the *biceps brachii* muscle and the *gastrocnemius medialis* muscle (Fig. 1).

**Fig. 1 Fig1:**
[figure not shown]
ELASTOPELV study design, inclusion criteria and data collected

### Setting

The study will take place in the department of Obstetrics and Gynecology of the Poitiers University Hospital, Poitiers, France.

### Population

The inclusion criteria are as follows: women older than 18 years, volunteers, nulliparous, with a normal singleton pregnancy, and who benefit from health insurance.

The exclusion criteria are as follows: women with previous vaginal and/or cesarean delivery, women with a personal history of pelvic floor disorders (urinary incontinence, anal incontinence, pelvic organ prolapse), women with a body mass index (BMI) higher than 35 kg.m^− 2^, women with chronic muscular disease, women requiring admission into a psychiatric unit, women under judicial protection, and women unable to understand the French language.

If an included woman has a pregnancy who became pathological (define by the necessity of follow-up into pathological pregnancies consultations and/or admission in pathological pregnancies unit) she will no longer participate to the study and no data will be collected after this event. If a woman wants to stop its participation, no more data will be collected.

### Power calculation

This study deals with exploratory data with an absence of previous data that would allow a power calculation. Furthermore, the main endpoint of the project is descriptive (to describe changes in the elastic properties of the *levator ani* muscle during pregnancy), and, therefore, an a priori power calculation does not appear necessary. We aim to obtain and study the data from at least 50 women. We considered this sample size in part due to previous studies that reported an increase in *levator hiatus* area and ligamentous laxity during pregnancy, as well as changes in the intrinsic biomechanical characteristics of pregnant women, from between 20 to 50 women [17–19]. We estimate that 20% of the women will be excluded during pregnancy because of a complicated pregnancy and/or their own choice, leading to an objective of 60 inclusions.

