#### Plan of analysis

We will describe the anthropometric and sociodemographic characteristics of the included women. Age, BMI and term of pregnancy will be reported as the mean and standard deviation (SD). For all the other analysis, we will only consider data about women who completed the three planned visits. For each trimester, we will only collect continuous variables, which will be reported as the means and SDs. Changes in these variables during pregnancy will be investigated using a Friedman test. Obstetric data will be reported as the means and SD for continuous variables and as percentages and frequencies for categorical variables.

Regarding the study endpoints, we will first report the main outcome of this study, which consists of the changes in the pelvic floor muscle’s shear modulus across the pregnancy. Then, we will report the changes in all other measured pelvic floor-related parameters (POP-Q measurements, ultrasound B-mode measurements). We will look for an association between the shear modulus of the levator ani muscle and clinical (POP-Q measurements) and ultrasound B-mode assessments at each trimester using a Spearman correlation coefficient calculation. Second, we will report the changes in the shear modulus of the *biceps brachii* and *gastrocnemius medialis* muscles to look for changes between the different investigated locations. Third, we will look for an association between the shear modulus of the pelvic floor muscles (*levator ani* and external anal sphincter) and both the mode of delivery (vaginal or cesarean delivery) and perineal tear occurrence using univariate analysis. Variables with a level of significance greater than *p* < 0.15 in univariate analysis will be included in the multivariate analysis using a logistic regression. We will perform statistical analysis with Stata software (version V14IC; Stata Corporation, College Station, TX, USA). For all analyses, significance will be considered for *p* < 0.05, and we will calculate odds ratios (ORs) with 95% confidence intervals when appropriate.

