## Discussion

### Short summary of the study

It is difficult to predict the outcome of severe perineal trauma (OASI and/or levator avulsion) at childbirth, as there is a strong potential of an alteration of the woman’s health. One hypothesis to optimize the efficiency of risk prediction is to consider the intrinsic biomechanical characteristics of women’s pelvic floors. Such an approach may allow an individualized risk assessment personalized information for each woman. Our prospective, monocentric, longitudinal study will include 60 nulliparous pregnant women. Three visits are planned in this protocol (one per trimester of pregnancy) and will include clinical (POP-Q) and ultrasound assessment of the pelvic floor, SWE assessment of the pelvic floor muscles (*levator ani,* external anal sphincter) and the *biceps brachii* and *gastrocnemius medialis* muscles. Finally, data about the mode of delivery (cesarean section or vaginal delivery) and the occurrence of perineal tears will be collected. The main endpoint will be to describe the changes in the elastic properties of the pelvic floor muscles across pregnancy. The secondary endpoints will be to look for an association between SWE measurements of the *levator ani* muscle and clinical and ultrasound perineal assessments, to compare muscular changes during pregnancy among the pelvic floor muscles and the *biceps brachii and gastrocnemius medialis* muscles and to look for an association among the elastic properties of the pelvic floor muscles, the mode of delivery and the occurrence of perineal tears.

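### Sixty inclusions with the protocol's own 20% loss are expected to leave 48 women, not the stated minimum of 50

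*Protocol article*

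**What the plan says.** The Power calculation section explains that no earlier data allow a formal calculation and that, the main endpoint being descriptive, "an a priori power calculation does not appear necessary". It then gives three figures in sequence:

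- a target: "We aim to obtain and study the data from at least 50 women", justified in part by earlier studies of 20 to 50 women;
- a loss: "We estimate that 20% of the women will be excluded during pregnancy because of a complicated pregnancy and/or their own choice";
- a result: "leading to an objective of 60 inclusions".

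The Short summary of the study, in the Discussion, repeats the result: "Our prospective, monocentric, longitudinal study will include 60 nulliparous pregnant women".

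Two other sections decide what happens to the women who are lost. Under Population, no further data are collected once a pregnancy becomes pathological or a woman withdraws. Under Plan of analysis, after the description of the included women, the rule is: "For all the other analysis, we will only consider data about women who completed the three planned visits". The article mentions no replacement of lost women and gives no other loss rate.

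**The concern.** An inclusion target derived from a required number and a loss rate should return the required number when the loss is applied to it. Here it does not. The women excluded during pregnancy are women already included, so the 20% is a share of inclusions, and taking 20% off 60 leaves fewer than 50. Because analysis is limited to women with all three visits, partial data from those lost cannot make up the difference.

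What is at stake is whether the sample-size paragraph is consistent with itself. With no power calculation, the target of 50 and its inflation to 60 are the protocol's argument for its size. If recruitment and retention both go exactly as planned, the report will show 48 women against a published minimum of 50, and the study will seem to have fallen short when it did what was planned.

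**Working it through.** **Inputs**, all from the Power calculation section: target of analysed women N = 50; loss d = 0.20; stated inclusions 60. The restriction to women with three visits comes from the Plan of analysis.

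**1. Reproducing the stated figure.** Adding 20% of the target to the target:

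N × (1 + d) = 50 × 1.20 = 60.

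This matches exactly, so it is the apparent source. The article shows no formula, and rounding to a convenient number is also possible.

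**2. Applying the loss to the stated inclusions.**

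60 × (1 − d) = 60 × 0.80 = 48, which is 2 below 50 (2 / 50 = 4%).

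**3. Inclusions that match 50 in expectation.**

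N / (1 − d) = 50 / 0.80 = 62.5, rounded up to 63.

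Check: 62 × 0.80 = 49.6 (short); 63 × 0.80 = 50.4 (sufficient). The stated figure is 3 inclusions lower.

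**4. Loss rate at which 60 would suffice.**

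1 − 50 / 60 = 0.167.

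Sixty inclusions leave 50 women only if loss is at most 16.7%, a rate the article does not state.

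**5. Chance of reaching 50.** This step needs an assumption that the article does not make: each woman is lost independently with probability 0.20. The exact binomial probability of at least 50 completers is then:

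| Inclusions | Expected completers | P(at least 50) |
|---|---|---|
| 60 | 48.0 | 0.32 |
| 63 | 50.4 | 0.62 |

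So 63 matches 50 as an expected number but would still miss it more than one time in three.

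**6. What two women are worth.** As a yardstick only, take the 95% confidence interval half-width for a mean paired change, t(0.975, n − 1) / √n, in units of the standard deviation of the change:

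- n = 48: 0.290
- n = 50: 0.284

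The difference is 0.006 standard deviations. The protocol plans a Friedman test rather than this interval, so the figures only indicate scale.

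**The case against.** The best defence is that the 50 carries little weight. It is worded as an aim. It does not come from a power or precision requirement, and it rests in part on earlier studies of 20 to 50 women, a range in which 48 also lies. The 20% is an estimate, and a loss of 16.7% would reconcile all three numbers. By the yardstick above, two women fewer make no noticeable difference. All of this stands, and it is why the correction is minor.

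It does not remove the inconsistency. The article states 20%, not 16.7%, and presents 60 as following from that rate. Reading the 20% as a share of the 50 completers would rescue the 60, but the text describes women excluded in the course of pregnancy, who are part of those included.

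Three stronger readings are tempting and should be resisted:

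- A reader might infer that the study is too small for its purpose. The documents do not support this: the main endpoint is descriptive, and no stated requirement fails at 48.
- A reader might infer that 50 is the protocol's only quantitative design figure, which would make the slip more serious. It is not. The protocol also fixes three visits with gestational windows, three measures per condition, thresholds of 0.15 and 0.05 for p, and inclusion and study durations of 18 and 24 months.
- A reader might infer that 63 inclusions would secure 50 as a firm minimum. They would match it only in expectation, with about a 62% chance of reaching it under independent 20% loss.

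The summary in the Discussion is not a second error. It repeats 60 and agrees with the Power calculation section.

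**Conclusion.** The inconsistency is real, and it is small. On the protocol's own figures, 60 inclusions are expected to give 48 women with three visits, two below the stated minimum; the inclusion figure that matches 50 in expectation is 63. This rests on two readings, both well supported by the text: that the 20% applies to included women, and that those lost are neither replaced nor analysed. The expected count of 48 needs no further assumption. The probabilities of 0.32 and 0.62 do, since they take losses as independent at exactly 20%, and the article gives no basis for so precise a rate. No planned analysis or conclusion is put at risk; the sample-size statement needs to be made consistent.

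**What to change.** Change one sentence in the Power calculation section to say that 60 inclusions, with an expected loss of 20%, are expected to give about 48 women with three completed visits. It may help to add that 60 would give 50 only if loss did not exceed 16.7%. This needs no extra recruitment, and the Discussion summary can stay at 60. The only cost is a slightly less favourable expected number.

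If the sponsor prefers to keep 50 as the expected number, raise the inclusion figure to 63, describe 50 as expected rather than assured (63 × 0.80 = 50.4), and change the Discussion summary to 63. That costs three more inclusions.

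A statement of the precision obtainable with 48 women would be a reasonable addition, but it is optional and not needed to correct the arithmetic.

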### Recruiting procedure

Women eligible for the ELASTOPELV study will be informed about the study during their clinical consultations and/or ultrasound consultations during a normal pregnancy follow-up by their obstetrician and/or midwife. Eligible women interested in this study will be contacted by the investigator to obtain more information about the study and proceed with the inclusion if they give their free informed consent.

### Shear wave elastography principles

The novelty of the ELASTOPELV study is based on the use of SWE to investigate the in vivo elastic properties of the pelvic floor muscles of pregnant women. SWE allows a quantitative in vivo assessment of tissues during a classic ultrasound examination [15, 20]. An Aixplorer® device (Supersonic Imagine, Aix-en-Provence, France) will be used. A remote mechanical perturbation is applied to the tissue using a specific ultrasound sequence to induce the propagation of a shear wave into the tissue of interest. Due to the ultrafast ultrasound acquisition, the wave’s propagation speed is measured perpendicular to the ultrasound beam. This shear wave speed propagation is linked with the elastic modulus of the tissue: the stiffer the tissue, the higher the wave’s propagation speed is [15, 20, 21]. The elastic properties of the tissue are reported as the Young modulus, which represents the link between a stress and a strain in an isotropic tissue (similar mechanical properties in all directions). Muscles are stiffer along the fiber direction and thus cannot be considered isotropic. Considering an isotropic solid, the Aixplorer device gives E (Young’s modulus) as a measurement with, E = 3 μ = ρV^2^. with μ the shear modulus, ρ the density, V the shear wave speed.

In anisotropic solid the eq. E = 3 μ is no more valid. So, measurements should be divided by a factor 3 to obtain measurement of the muscle shear modulus [15, 22]. A previous study has demonstrated that the shear modulus is strongly and linearly related to the Young modulus, which supports the relevance of shear modulus measurements obtained with the Aixplorer® device for the study of muscle biomechanics [15, 23].

SWE is based on the hypothesis of a linear elasticity that is commonly assumed in both magnetic resonance elastography and ultrasound SWE. A lot of SWE studies analyzed the effects of loading on changes in muscle elasticity [15]. The effect of nonlinear elasticity should be studied in the future.

